## 4 STUDY POPULATION

### 4.1 Number of subjects to be studied

80 subjects are required per treatment group allowing for drop-outs: a total of 160 patients need to be randomised and start treatment (EndoBarrier device or diet and exercise) at visit 4.

### 4.2 Inclusion criteria

1. Age 18-65 years (male or female)
2. T2DM for at least 1 year (HbA1c 7.5-11.0% = 58-97 mmol/mol)
3. On oral T2DM medications (metformin is allowed, but not required)
4. BMI 30-50 kg/m^2

### 4.3 Exclusion criteria

1. Language barrier, mental incapacity, unwillingness or inability to understand and be able to complete questionnaires
2. Non-compliance with eligibility criteria
3. Females of childbearing potential who are pregnant, breast-feeding or intend to become pregnant or are not using adequate or reliable contraceptive methods
4. Evidence of absolute insulin deficiency as indicated by clinical assessment, a long duration of T2DM and a fasting plasma C-peptide of <333pmol/L
5. Current use of insulin
6. Previous diagnosis with Type 1 DM or a history of ketoacidosis
7. Requirement of NSAIDs (non-steroidal anti-inflammatory drugs) or prescription of anticoagulation therapy during the implant period
8. Current iron deficiency and/or iron deficiency anaemia
9. Symptomatic gallstones or kidney stones at the time of screening
10. History of coagulopathy, upper gastro-intestinal bleeding conditions such as oesophageal or gastric varices, congenital or acquired intestinal telangiectasia
11. Previous GI surgery that could affect the ability to place the device or the function of the implant
12. History or presence of active H. pylori (if subjects are randomised into the EndoBarrier arm and have a history or presence of active H. pylori – tested during study visit 2 - they can receive appropriate treatment and then subsequently enrol into the study)
13. Family history of a known diagnosis or pre-existing symptoms of systemic lupus erythematosus, scleroderma or other autoimmune connective tissue disorder
14. Severe liver impairment i.e. AST, ALT or gGT >4 times upper limit of the reference range or kidney impairment i.e. estimated Glomerular Filtration Rate (GFR) < 45 ml/min/1.73m^2
15. Severe depression, unstable emotional or psychological characteristics (indicated by Beck Depression Inventory II score >28)
16. Poor dentition and inability to adequately chew food
17. Planned holidays up to three months following the EndoBarrier Implant
18. Previous EndoBarrier implantation

|                                                                                   |                                                                                                  |                                           |                                                             |                                                  |
|-----------------------------------------------------------------------------------|--------------------------------------------------------------------------------------------------|-------------------------------------------|-------------------------------------------------------------|--------------------------------------------------|
| [figure not shown] | Title:
EndoBarrier TM
Gastrointestinal Liner
Diabetes Trial | Protocol No:
Version 5.0 | Sponsor:
Imperial College
London | Date:
5th March 2018 |
|-----------------------------------------------------------------------------------|--------------------------------------------------------------------------------------------------|-------------------------------------------|-------------------------------------------------------------|--------------------------------------------------|

19. Metal implant unsuitable for MRI scanning and claustrophobia as contraindications for MRI scans (sub-group 1 - fMRI study only)
20. Vegetarian, vegan, gluten or lactose intolerance as unsuitable for fMRI food picture paradigm (sub-group 1 – fMRI only)

#### 4.4 Withdrawal criteria

Subjects may be withdrawn from the study at the discretion of the Investigator or Sponsor due to a safety concern or if judged non-compliant with trial procedures.

A subject must be withdrawn from treatment if the following applies:

1. Subject chooses to withdraw from the study at any time
2. Adverse Event requiring device explant
3. Pregnancy or intention of becoming pregnant

Reasons for withdrawals and discontinuation of any subject from the protocol have to be recorded.

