## **6.7 MRI safety and protection of patients**

The MRI scanner contains a very strong magnet. Therefore, individuals may not be able to have the MRI if they have any type of metal implanted in their body, for example, any pacing device (such as a heart pacer), any metal in their eyes, or certain types of heart valves or brain aneurysm clips. Magnetic resonance imaging metal check list will be completed at each visit to ensure compatibility with MRI scanning.

There is not much room inside the MRI scanner. Some people may be uncomfortable if they do not like to be in close spaces (“claustrophobia”). This is therefore an exclusion criterion for recruitment to the MRI study. If subjects experience discomfort within the scanner despite the measures taken to ensure patient comfort, the patient may request immediate cessation of the procedure with withdrawal from the scanner by ringing the patient alarm bell.

The MRI produces a “hammering noise” but subjects wear earplugs and headphones to prevent discomfort or damage to hearing.

At fMRI study visits, anatomical brain scans will be collected. It should be noted that these scans cannot be viewed as a comprehensive health screening procedure. However, very rarely, unexpected information can be detected which may warrant further investigation. In this event, a report will be sent to the patient's GP, who will arrange further tests and coordinate further care. Significant structural anatomical abnormalities will also preclude the subject from further

|                                                                                   |                                                                                                  |                                           |                                                             |                                                  |
|-----------------------------------------------------------------------------------|--------------------------------------------------------------------------------------------------|-------------------------------------------|-------------------------------------------------------------|--------------------------------------------------|
| [figure not shown] | Title:
EndoBarrier TM
Gastrointestinal Liner
Diabetes Trial | Protocol No:
Version 5.0 | Sponsor:
Imperial College
London | Date:
5th March 2018 |

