## 7.2 Early Discontinuation of Individual Subjects

Subjects may discontinue study treatment (EndoBarrier) for the following reasons:

- At the request of the subject.
- If the investigator considers that a subject's health will be compromised due to adverse events or concomitant illness that develops after entering the study.

Any subjects who withdraw from the study that have the device implanted will have the device removed as soon as it can be arranged. Subjects that have the device removed before Month 3 will return for the End of Treatment/Months 12 (visit 11). Subjects that have the device removed after Month 3 will return for the End of Treatment/Month 12 (visit 11), Month 15 (visit 12), Month 18 (visit 13) and Month 24 (visit 15) post explant follow-up visits.

All subjects (including both control and device arm) who withdrew from the study early (either prior or after their treatment started – visit 4), and where no follow-up visit has been agreed or arranged as part of the previous protocol version (V4.1), will be contacted over the phone by the study team to ask for their permission (verbal consent documented by the study doctor using a specific form filed in the medical records) to perform a short telephone consultation at Month 24 (equivalent to visit 15). Data collected during this visit will include:

- HbA1 (provided through their last routine appointment at their GP)
- Body weight in kg
- Adverse events (section 6)
- Medical history/medication changes (section 5.5.4)

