Conservatively, it was estimated that 15% of patients in the control arm will achieve the target but believe this to be an overestimate. The Steno study  is the best quality randomised study (80 patients in each arm) into the effect of best medical therapy published to date and demonstrated over an average 7.8 years significant improvements in HbA1c amongst those having intensive medical therapy from 8.4+/- 1.6 to 7.7+/-1.2, but no change in HbA1c amongst those continuing with standard medical therapy. This study defines the very best that could realistically be achieved in the control arm, but expect there to be very little if any change in this group. The reporting of HbA1c as an outcome measure was not in accordance with the newly defined IDF criteria, but considering the small average reduction achieved in the Steno study, it will be assumed that a target of 15% of patients reaching the endpoint is a conservative estimate. Company data on the small number of patients who have reached a year with the device in place suggest that 40% will achieve this target.

According to our own experience with the device in the commercially sponsored study, up to 30% of patients in the treatment group may have the device removed early. Nevertheless other commercially sponsored (unpublished) studies of this device have achieved lower explant rates ([name] – GI Dynamics). We have therefore diluted the treatment effect from 40% vs. 15% to 35% vs. 15% achieving the target of 20% reduction in HbA1c for treatment arm vs. standard arm. 73 patients per group will give 80% power to detect a significant effect. Adding 10% loss of follow-up increases the sample size to 80 per group.

The dilution was calculated starting from the assumption that 40% of patients with the device will reach the target (this estimate is based on company data based on diabetic patients in the same range of BMI as in the present proposal). If 30% of patients in the treatment group need to remove the device early but remain available for follow-up, in the worst case scenario, the proportion reaching the target is the same as in the control group, bringing the estimate for the treatment group to 32.5%. However most of them will keep the device for some time, having some benefit, so it is plausible to assume that the estimate is higher than 32.5%.

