## 8.2 Data Analysis

Patient characteristics will be summarized. Summaries of continuous variables will be presented as means and standard deviations if normally distributed, and as medians and inter-quartile ranges for skewed data, whilst categorical variables will be presented as frequencies and percentages. The difference between the two study groups in the proportion of patients achieving substantial improvement in the metabolic syndrome both at 12 and 18 months will be analysed using logistic regression adjusting for the stratification variables (BMI groups and sites). Analysis of secondary outcomes will be conducted using standard statistical procedures applicable to categorical or continuous data as appropriate. For missing values we will explore the pattern and the extent of missingness and we will carry out an appropriate form of multiple imputation if required. The analysis will be performed according to the intention to treat principle. All statistical tests will be two-tailed with a 5% significance level.

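### Section 4.4 lets the investigator or sponsor end a patient's study participation, in either arm, without requiring that outcomes still be collected

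*Protocol*

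**What the plan says.** Section 4.4 uses two levels of withdrawal. The first is discretionary and concerns the study: "Subjects may be withdrawn from the study at the discretion of the Investigator or Sponsor due to a safety concern or if judged non-compliant". The second is mandatory and concerns treatment: "A subject must be withdrawn from treatment if the following applies". That second list includes "Adverse Event requiring device explant", but also a patient's own choice to leave the study, so the two levels are partly mixed. Section 4.4 asks for reasons to be recorded. It does not say whether outcomes are still collected after a discretionary withdrawal.

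Section 5.2 tells patients their arm at Visit 2, one arm then receives an implant, and no blinding is described.

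Section 7.2 says: "Any subjects who withdraw from the study that have the device implanted will have the device removed as soon as it can be arranged". It then sets return visits: Visit 11 (Month 12) if the device came out before Month 3, and Visits 11, 12, 13 and 15 if it came out later. For early withdrawals in either arm with no follow-up arranged, it adds a telephone contact at Month 24. This needs the patient's permission and takes HbA1c from the last routine GP appointment.

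Section 8.1 builds its device-arm rate on patients who "need to remove the device early but remain available for follow-up", and counts withdrawals after Visit 4 within the planned drop-out. Section 8.2 states: "The analysis will be performed according to the intention to treat principle", with multiple imputation if required.

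Section 6.7, on MRI safety, adds: "Significant structural anatomical abnormalities will also preclude the subject from further" participation in the study.

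**The concern.** Intention to treat needs the outcome of every randomised patient as far as it can be had. A clause that lets staff who know the allocation close a patient's participation, for reasons tied to how treatment is going, creates missing outcomes that could have been avoided. The reasons can differ by arm. A safety concern arises more readily with an implant, since section 1.5 names bleeding, migration and pain as the usual causes of removal. Non-compliance in either arm may go with poor glycaemic response. If those removed respond differently from those kept, the comparison of observed patients is distorted, and imputation helps only as far as recorded data explain who left.

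The section 8.1 calculation is also exposed. It allows 10% loss and separately expects up to 30% early removal, on the footing that those 30% are still measured.

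**Working it through.** **The plan's own figures**

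Inputs from sections 8.1 and 8.2: 35% v 15%, 80% power, two-sided 5%, 73 per group, raised to 80 for 10% loss. Early removal is 30%. Response is 40% with the device kept, and 15, 23 and 31% in equal thirds of those explanted.

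- Sample size (two proportions, pooled variance): n = [1.96 × √(2 × 0.25 × 0.75) + 0.842 × √(0.35 × 0.65 + 0.15 × 0.85)]² / 0.20² ≈ 72.4, so 73. This reproduces.
- Diluted device rate: 0.7 × 40% + 0.1 × (15% + 23% + 31%) = 34.9%, stated as 35%. This reproduces.
- Mean response among explanted patients: (15 + 23 + 31) / 3 = 23%.

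The sample size has no arithmetic error. The 35% does depend on explanted patients being measured.

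**What follows if some explanted patients are lost**

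Of 80 device patients, 0.30 × 80 = 24 are explanted early and 56 keep the device. The share of the 24 who are withdrawn and lost is not in the protocol, so it is varied as an assumption. The other 10% loss is taken to be unrelated to outcome. With e explanted patients retained:

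- completer rate = (56 × 0.40 + e × 0.23) / (56 + e)
- device-arm loss = 1 − 0.9 × (56 + e) / 80

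| Share of 24 lost | e | Completer device rate | Shift from 34.9% (points) | Device-arm loss |
|---|---|---|---|---|
| 0% | 24 | 27.92 / 80 = 34.9% | 0 | 10% |
| 25% | 18 | 26.54 / 74 = 35.9% | 1.0 | 17% |
| 50% | 12 | 25.16 / 68 = 37.0% | 2.1 | 24% |
| 100% | 0 | 22.40 / 56 = 40.0% | 5.1 | 37% |

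If lost explants were instead counted as non-responders (not the plan's stated method), the device rate would be 33.2, 31.5 or 28.0% for 25, 50 or 100% lost. Power with 72 evaluable per arm would fall from 79% to 73, 65 or 48%.

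**Does section 7.2 secure the outcome?**

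Table 4 schedules HbA1c at Visits 1, 5, 7, 8, 9, 10, 12, 13 and 15, and not at Visit 11. Section 8.2 analyses 12 and 18 months.

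- Removal before Month 3: Visit 11 only, so neither time point has a scheduled HbA1c after explant.
- Removal after Month 3: Visits 11, 12, 13 and 15. Month 18 is covered at Visit 13. The first HbA1c at or after Month 12 is at Month 15, because Visit 10 (11.5 months) is not among the listed visits.
- Controls withdrawn as non-compliant: no return visits are set. The Month 24 call, if permitted, gives a GP value that answers neither time point.

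**The case against.** The strongest reply is that the protocol already does what is asked. Section 4.4 itself makes explant for an adverse event a withdrawal from treatment. Section 7.2 attaches return visits even to patients with an implant who leave the study, and adds a contact for both arms. The section 8.1 assumption is therefore what section 7.2 sets out to deliver. Withdrawals after Visit 4 are budgeted as drop-outs. Intention to treat with multiple imputation is stated, the imputation model is left open, and HbA1c values from before withdrawal may exist.

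Most of this stands. It rules out reading section 4.4 as an instruction to drop device failures. It also rules out treating the 40% figure as expected: that needs every one of 24 explants to be lost, and 30% removal is itself an upper estimate. Nor can it be said that imputation must fail.

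What the reply does not answer is the discretionary clause itself. Section 4.4 neither refers to section 7.2 nor requires further data, the return schedule does not cover controls, and the scheduled visits miss HbA1c where it is needed.

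On section 6.7, the study may well mean the MRI study. Such findings are described as very rare and both arms are scanned, so no between-arm bias is shown. The wording is ambiguous and no more.

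**Conclusion.** The point holds as a gap between sections: section 4.4 permits discretionary withdrawal from the study in either arm, with allocation known and no duty to continue outcome collection, and section 7.2 repairs this only in part. With a quarter to a half of expected explants lost, the completer device rate would be overstated by about 1 to 2 points and device-arm loss would be 17 to 24% against 10% planned. The full-loss case (5 points, 37%) is an extreme that section 7.2 is written to prevent. These figures rest on the protocol's response rates, on 30% removal, and on an assumed share lost.

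A reader might infer that section 4.4 removes device failures from the trial, or contradicts intention to treat and section 8.1 outright. The documents do not support that. Explant is a treatment-level event with planned visits, and missing outcomes do not take a patient out of the analysis population. Nor is the direction of bias settled, because removing non-compliant controls who respond poorly would raise the observed control rate and work the other way.

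**What to change.** - **Section 4.4:** separate stopping treatment from ending study follow-up. Remove non-compliance as a ground for ending follow-up. State that only withdrawal of consent ends outcome collection, in either arm. Move the patient's choice to leave the study out of the treatment list.
- **Sections 7.2 and 8.1:** reconcile them with section 4.4, so that the patients section 8.1 counts on are those section 7.2 brings back, and so that controls who stop complying are covered too.
- **Table 4:** add HbA1c at the Month 12 return visit (Visit 11) for patients explanted early.
- **Section 6.7:** clarify that a scan finding ends further participation in the MRI sub-study and does not by itself end follow-up in the randomised trial.

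The cost is a wording amendment and one routine blood test at an existing visit. Some non-compliant patients must still be invited to visits already planned for them. No rule on when treatment stops needs to change.

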## 5 VISIT PROCEDURES, MEASUREMENTS AND ASSESSMENTS

### 5.1 Recruitment and Screening

*Participants will be identified from a number of areas which include:*

- **Registers of patients with diabetes who have consented to be contacted about future research including DARE (Diabetes Alliance for Research in England REC 2002/7/118)**

The team responsible for a register will search the system to identify suitable participants and send out an invitation letter and participant information sheet. Interested patients will be asked to contact the research team directly to find out more about the study. No patient details will be passed on to the study team.

- **Hospital or GP patient databases/notes review (Research Site or Participant Identification Centre)**

This activity will be completed by the routine care team. The medical records may be reviewed by members of the routine care team to pre-screen whether the patient may potentially be eligible for the study before the patient is approached about the study by a member of the routine care team (hospital or GP).

|                                                                                   |                                                                                                  |                                           |                                                             |                                                  |
|-----------------------------------------------------------------------------------|--------------------------------------------------------------------------------------------------|-------------------------------------------|-------------------------------------------------------------|--------------------------------------------------|
| [figure not shown] | Title:
EndoBarrier TM
Gastrointestinal Liner
Diabetes Trial | Protocol No:
Version 5.0 | Sponsor:
Imperial College
London | Date:
5th March 2018 |
|-----------------------------------------------------------------------------------|--------------------------------------------------------------------------------------------------|-------------------------------------------|-------------------------------------------------------------|--------------------------------------------------|

Potential participants will be sent an invitation letter, participant information sheet and study summary and asked to complete a reply slip, telephone or send an email to the research team. If the subject is eligible they can contact the research team to arrange an appointment for a screening visit at Imperial College London (St. Mary's Hospital) or University of Southampton (NIHR Wellcome Trust Clinical Research Facility (WTCRF)).

- **Face to face approach during routine clinic visits (Research Site or Participant Identification Centre)**

Potential participants will be identified from the clinic lists. Consultants/GPs will review the upcoming clinic list and flag any participants that should not be approached. The nurse or doctor routinely involved in the patients care will send an invitation letter ahead of the clinic or approach participants face to face during the clinic to provide the Participant Information Sheet. The nurse or doctor routinely involved in the patients care will inform patients they can contact the research team if they are interested in partaking in the study.

- **Other research studies within Imperial College, Imperial NHS Trust and the Local Clinical Research Network (LCRN)**

Other research studies run at Imperial College, Imperial NHS Trust and the LCRN can speak to and provide further information about our trial to participants who were ineligible, withdrawn or excluded from their study but consented to be contacted for possible participation in future research studies.

- **Adverts, news stories, posters, information leaflets and business cards in public areas, newspapers, websites, GP surgeries and hospital clinics areas and support groups**
- **Diabetes, Obesity and other Support groups**
- **Study websites**
- **Social media websites**

Advertisements / news stories / trial websites etc. will only contain essential documentation approved by the ethics committee (patient information sheet, trial contact details etc.). We may set up social media pages such as Twitter / Facebook which will contain basic trial contact details and referral to the website.

Members of the research team may attend support group meetings by invitation to discuss the study. Leaflets will be made available to members.

|                                                                                   |                                                                                                  |                                           |                                                             |                                                  |
|-----------------------------------------------------------------------------------|--------------------------------------------------------------------------------------------------|-------------------------------------------|-------------------------------------------------------------|--------------------------------------------------|
| [figure not shown] | Title:
EndoBarrier TM
Gastrointestinal Liner
Diabetes Trial | Protocol No:
Version 5.0 | Sponsor:
Imperial College
London | Date:
5th March 2018 |
|-----------------------------------------------------------------------------------|--------------------------------------------------------------------------------------------------|-------------------------------------------|-------------------------------------------------------------|--------------------------------------------------|

